## 8 Assessment of Safety

### Risks and benefits

This is a low risk study. Exercise during cancer treatments has been widely studied, reported as a safe intervention for individuals with cancer and is recommended as part of usual clinical care (Cormie 2018). Participants may experience some post exertional malaise and/or delayed onset muscle soreness, but the research team, trained physiotherapists, will ask about these symptoms every week and modify the program as required and also liaise with the treating medical team. The main risk to the participants in this study is inconvenience relating to the time and travel expense associated with attending the study assessments.

We will be assessing quality of life surveys. It is possible that participants will report low or reducing quality of life and/or depressive symptoms. Should these be identified we will recommend and refer the participant to the psychology support services, through the usual referral pathways within the Breast Clinic.

Regarding benefits, those allocated to the experimental group will receive the SMART program. We hope that this program will optimise participation in structured exercise and produce sustained improvements in health-related quality of life. If this is the case, we will endeavour to implement a similar program as part of routine physiotherapy care at RPH in the future.

Participants will be offered vouchers in compensation for travel costs for the face to face appointments and the time taken to complete the study assessments. These vouchers will be valued at \$15 for travel cost compensation and \$20 for time compensation to complete the assessments.

### Safety

Physiotherapists are trained in providing exercise prescription for a wide variety of health conditions. All RPH physiotherapy staff have annual training to stay up-to-date with departmental emergency procedure training specific to gym based exercise sessions and telehealth appointments run through the RPH. Nevertheless, during each weekly contact, for participants in both groups, we will record (in REDCap) for any adverse events and classify these as minor (i.e. resolve without any need for a medical review) or non-minor (i.e. those that warranted a medical review).

Examples of minor adverse events might include episodes of dizziness or nausea during exercise or the muscle soreness and generalise malaise on completion of an exercise session. Example of non-minor adverse events might include an injurious fall or cardiac event. These will be discussed at the DSMB.

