**Rehabilitation:** The target behaviour to work towards participation in 150 minutes moderate intensity aerobic exercise per week as well as two resistance sessions, as per the above ACSM guidelines.

**Telehealth supported:** A physiotherapist will offer supervised weekly sessions with each participant via telehealth (or in person at RPH) to supervise exercises, adjust their programs as needed and to implement behaviour change strategies to aid uptake of optimal exercise habits throughout their BC treatment. Participants will also receive email or phone prompts to complete their program on days according to their exercise routine.

Those randomised to the control group will receive usual care. This comprises education regarding the importance of exercise during cancer treatment, a pamphlet and information regarding appropriate off-site exercise groups. In addition, the control group will receive a phone call from the research team once a month. During this phone call, information regarding healthcare utilisation will be collected and participants will receive generic encouragement to stay active during over the 16-week period. The phone call in the control group is important to reduce the potential confounding effect of increased contact (attention) with healthcare professionals in the experimental group.

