### 2) Weekly sessions with a physiotherapist

Once a week, participants will meet with a physiotherapist, either in person (at RPH) or via telehealth. This session will be approximately one-hour in duration. During this session, (i) the participant and physiotherapist will reflect on the achievement of the goals set towards the target behaviour for the previous week, (ii) the participant will perform a supervised exercise session that comprises aerobic and resistance exercise and the physiotherapist will provide feedback and reassurance and, (iii) the participant and physiotherapist will plan the exercise training sessions for the following week.

Goal setting will be individualised and consider; (i) participant's preferences and, (ii) the timing and severity of the likely or experienced side effects of the BC treatment. Goals will be agreed upon that are Specific, Measurable, Achievable, Relevant and Time-bound (SMART). An example of an exercise plan is included in Table 1 below.

Table 1: Example exercise plan

| My exercise plan for week beginning 03/06/24: |      |                                                                                                                     |
|-----------------------------------------------|------|---------------------------------------------------------------------------------------------------------------------|
| Monday                                        | 2pm  | Gym session 60 mins (20-30 mins aerobic, 30 mins resistance exercises). Refer to your online exercise prescription. |
| Tuesday                                       | 10am | Walk dog for 45 minutes (aim for heart rate of 120bpm)                                                              |
| Wednesday                                     |      | Walk dog for 45 minutes (aim for heart rate of 120bpm)
Chemo in the afternoon                                    |
| Thursday                                      | 10am | Gym session 60 mins (20-30 mins aerobic, 30 mins resistance exercises). Refer to your online exercise prescription. |
| Friday                                        |      | Day of rest                                                                                                         |

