## 6 Treatment of Participants

### Description and justification for treatments, interventions or methods to be utilised

Those randomised to the experimental group will receive the *SMART* exercise program, as discussed above. Those randomised to the control group will receive usual care. This comprises education regarding the importance of exercise during cancer treatment, a pamphlet/information regarding appropriate off-site exercise groups. Separate oncology physiotherapy provision for patients undergoing chemotherapy treatment involves education strategies and the option to attend a weekly exercise session in the physiotherapy gym. However, exercise intervention as part of routine physiotherapy care for this patient group at RPH is currently through an “opt-in” system and resultant uptake of this service is low. In addition, the control group will receive a phone call from the research team once a month. During this phone call, information regarding healthcare utilisation will be collected and participants will receive generic encouragement to stay active during over the 16-week period.

The trial will run over a three-year period, with recruitment commencing in early 2024. Each participant will provide informed consent, after which they will complete a baseline assessment. On completion of these baseline assessments, participants will be randomised to either the experimental or control group and complete a 16-week intervention phase. Thereafter, all participants will complete a suite of re-assessments, (i) mid-way through the intervention phase, (ii) on completion of the intervention phase and, (iii) 12 months following randomisation.

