## OTHER VARIABLES

**Descriptive variables** will be recorded such as age, sex, body mass index, employment status, co-morbid conditions, stage of cancer and details of cancer treatment.

**Healthcare utilisation and adherence with exercise** will be assessed in both groups. In the control group, this will be documented during the monthly phone calls and exercise diaries. In the experimental group, this will be monitored by asking each participant during the weekly supervised sessions and also using exercise diaries (see Section 4, Monitoring). Regarding healthcare utilisation, we will ask each participant to recall the number of; (i) visits to the Emergency Department, (ii) inpatient admission days, (ii) outpatient appointments and, (iii) visits to any other healthcare provider (Y/N, who, number of visits). Regarding adherence with exercise, we will ask each participant to recall the number of minutes spent engaging in moderate or vigorous intensity exercise and details regarding any resistance exercise.

**Absenteeism and presenteeism** will be assessed using the iMTA productivity cost questionnaire (Bouwman 2015).

**Global rating of change** will be assessed by asking participants, on completion of the SMART exercise program, to indicate if their health-related quality of life or exercise tolerance had 'improved', 'worsened' or 'stayed the same'. Those participants who rated their walking ability as 'improved' or 'worsened' will then be asked to rate the degree of change on a seven-point scale (1 a little better to 7 a great deal better).

**Feasibility and acceptability** will be measured using; (i) Quantitative data from an acceptability and feasibility questionnaire, and (ii) qualitative data from exit interviews. These are described below:

*Quantitative data* will be collected using a questionnaire asking participants to rate their perceptions of the SMART exercise program (e.g., "*I thought the SMART exercise program was easy to understand*"). Participants can rate each item on a five-point scale (1 "*I don't agree at all*" to 5 "*I totally agree*"). Four open-ended items at the end of this questionnaire allow participants to include additional feedback (e.g., "*What did you like about the SMART exercise program?*").

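### Adverse events are said to be recorded weekly in both groups, but controls have only a monthly call, so minor events, healthcare use and, less so, exercise are at risk of differential ascertainment

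*Protocol*

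**What the plan says.** **Adverse events.** Section 8 (Safety) says that "during each weekly contact, for participants in both groups, we will record (in REDCap) for any adverse events". Events are graded minor or non-minor according to whether they needed medical review, and they are discussed at the DSMB.

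**Control contact.** Section 2 (Intervention) says "the control group will receive a phone call from the research team once a month", and Section 6 repeats this. On content, Section 6 says: "During this phone call, information regarding healthcare utilisation will be collected and participants will receive generic encouragement to stay active". Adverse events are not listed.

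**SMART contact.** Section 4 says: "Once a week, participants will meet with a physiotherapist, either in person (at RPH) or via telehealth". Under Monitoring, as an ingredient of the SMART program, participants also receive heart rate monitors and REDCap questionnaires about side effects. Neither is described for controls.

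**Healthcare use and exercise.** Section 7 (Other variables) says of the experimental group that "this will be monitored by asking each participant during the weekly supervised sessions and also using exercise diaries". For controls it says: "In the control group, this will be documented during the monthly phone calls and exercise diaries". Both items rely on recall: "Regarding healthcare utilisation, we will ask each participant to recall the number of" visits and admission days, and exercise minutes are asked for in the same manner.

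**Timing table (Section 7, Efficacy assessment).** Participation in exercise and healthcare utilisation are each marked in the weekly column, with no distinction between groups.

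**Use of the data.** Exercise adherence is among the between-group secondary outcomes at 16 weeks (Sections 3 and 9). Healthcare utilisation is descriptive only. Section 4 (Bias) says that blinded assessors carry out all assessments after randomisation.

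**The concern.** The Safety section assumes a weekly control contact that no other part of the protocol provides. As written, the control-group procedure for adverse events cannot be carried out, and the one contact that does exist has no stated adverse-event content.

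If the trial runs on the contacts that are actually scheduled, the groups differ in four respects that can alter counts without any difference in true rates: how often people are asked, how far back they must remember, who asks, and what else prompts them. In the SMART group the questions are put during the supervised session, so by a physiotherapist who knows the allocation. That sits badly with the blinding statement.

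Two uses of the data are exposed. The DSMB reviews adverse events and may raise concerns about continuing the trial. Exercise adherence is a between-group outcome, and it also enters the moderator and mediation analyses.

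**Working it through.** The plan gives no figure for this point, so there is nothing to reproduce. The check sets the passages side by side, counts contacts, and then illustrates the effect under a stated assumption.

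**1. Collection by group, from Sections 2, 4, 6, 7 and 8**

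| | SMART | Control |
|---|---|---|
| Scheduled contact | Weekly session, in person or telehealth | Monthly phone call |
| Adverse events | Weekly (Safety) | Weekly claimed; no weekly contact exists; not in the stated call content |
| Healthcare use | Weekly, by recall | Monthly, by recall |
| Exercise | Weekly questioning and diary, plus heart rate monitor | Monthly questioning and diary |
| Side-effect questionnaires | Yes | Not described |
| Who asks | Physiotherapist running the session | Research team |

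For adverse events, the Safety section conflicts with Sections 2, 6 and 7. For healthcare utilisation, the timing table's weekly mark conflicts with the monthly control calls. For exercise, the weekly mark could be met in controls by the diary, so no contradiction is shown for that row.

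**2. Number of contacts and recall window over 16 weeks**

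- SMART: 16 / 1 = 16 contacts, window 1 week.
- Control: 16 / (52/12) = 16 / 4.33 = 3.7 calls, or 16 / 4 = 4 if every four weeks. The window is about 4.3 weeks.
- Ratio of contacts: 16 / 4 = 4, so roughly 4 to 1.

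These are scheduled contacts; attendance may be lower.

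**3. Illustration under an assumed recall decay**

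Assume equal true rates, events spread evenly over the interval, the same question asked at every contact, and recall that decays exponentially with half-life h weeks. With k = ln 2 / h and interval T, the share captured is (1 − exp(−kT)) / (kT).

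Example, h = 4: k = 0.1733.

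- T = 1: (1 − 0.841) / 0.1733 = 0.918.
- T = 4.33: kT = 0.751, and (1 − 0.472) / 0.751 = 0.703.
- Apparent ratio: 0.918 / 0.703 = 1.31.

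| Assumed half-life (weeks) | Captured, weekly | Captured, monthly | Apparent SMART:control ratio |
|---|---|---|---|
| 2 | 0.845 | 0.518 | 1.63 |
| 4 | 0.918 | 0.703 | 1.31 |
| 8 | 0.958 | 0.834 | 1.15 |
| 16 | 0.979 | 0.912 | 1.07 |
| 26 | 0.987 | 0.944 | 1.04 |

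Short half-lives suit easily forgotten symptoms, and long ones suit memorable events such as admissions. None of the half-lives comes from the protocol. The model also takes adverse events to be asked about at the monthly call, which the stated content of that call does not say.

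**The case against.** Much can be said for the plan. The primary endpoint uses the same questionnaires at the same times in both groups and is untouched. So are strength, walking distance, muscle mass and chemotherapy completion. Healthcare utilisation is descriptive, and no between-group test of adverse events is specified. Non-minor events are by definition those that needed medical review, so they depend less on prompting. The minor examples in the Safety section arise during or after exercise, so an excess in SMART could be partly real. For exercise, both groups keep a diary. All of this stands and limits the point.

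A reader might infer more than the documents support, in three ways:

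- **That SMART data are gathered face to face and control data only by phone.** Telehealth is an option for the weekly session, and the control diary is a second source for exercise.
- **That every between-group comparison of these items is biased.** The text supports a risk of differential ascertainment, greatest for minor events, and not a demonstrated bias in each comparison.
- **That a spurious rate ratio can be stated.** Any such ratio only restates the recall rate assumed, and the protocol gives none.

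These limits do not resolve the contradiction over weekly contact, or the roughly fourfold difference in scheduled questioning.

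**Conclusion.** The point holds in a limited form and should be fixed; it does not threaten the primary analysis. The Safety section and the healthcare-utilisation row of the timing table contradict the monthly control contact given in Sections 2, 6 and 7. The documents do not settle which is intended.

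If the scheduled contacts are followed, there are about 16 occasions to report in SMART against about 4 in control, with recall windows of 1 and about 4.3 weeks. Minor adverse events and recalled healthcare use are the most exposed. Exercise adherence is exposed to a lesser degree: the shared diary helps, but weekly questioning and heart rate monitors remain in one group only.

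The size is unknown. Under the assumed half-lives of 2 to 26 weeks and equal true rates, the apparent ratio runs from 1.63 down to 1.04, so it could be material for forgettable symptoms and negligible for memorable events.

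**What to change.** 1. Reconcile the Safety section and the timing table with the control contact described in Sections 2, 6 and 7, and state when and how adverse events are sought in each group.
2. For any between-group comparison of adverse events or healthcare use, use one identical REDCap form, with the same interval and recall window in both groups, collected independently of the treating physiotherapist. If healthcare use is to be described over 12 months, as Section 3 asks, continue the form on the same terms after week 16.
3. For exercise minutes and resistance sessions, keep the diary as the source, with the same format and completion schedule in both groups.
4. Tabulate separately the events found only through SMART weekly sessions or side-effect prompts, including in reports to the DSMB. The weekly records remain available for adapting the program.

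REDCap is already used to send out questionnaires, so the cost is a few minutes per participant per form and a protocol wording change. The change has to be prospective, because minor control events that were never asked about cannot be reliably recovered at analysis. If common collection is not adopted, reports should say that ascertainment was not comparable between groups.

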## Trial Termination

We will establish a Data Safety Monitoring Board (DSMB) of experienced researchers (n = 3), who are independent to the study group. This DSMB will meet after the successful recruit of each block of 50 trial participants. Progress of the trial participants (and any adverse events) and the changes in the primary outcome will be discussed. The DSMB will inform the study team of any concerns that would warrant discontinuation of the trial.

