### Adverse event reporting

Non-minor adverse events will be reported to the HREC within 48 hours.

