### Follow-up of Adverse Events

We will report any adverse events to the treating medical team as appropriate.

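### Adverse events are graded only by need for medical review, so serious or exercise-related events are not separated from cancer-treatment toxicity

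*Protocol*

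**What the plan says.** Under Safety (section 8), the scope of recording is wide: "for participants in both groups, we will record (in REDCap) for any adverse events". The rule for sorting the events has a single criterion, which is to "classify these as minor (i.e. resolve without any need for a medical review) or non-minor (i.e. those that warranted a medical review". The examples given for the minor class are "episodes of dizziness or nausea during exercise or the muscle soreness and generalise malaise on completion of an exercise session". For the other class the text reads "Example of non-minor adverse events might include an injurious fall or cardiac event".

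Three further provisions use these records:

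- Adverse event reporting: "Non-minor adverse events will be reported to the HREC within 48 hours".
- Trial Termination, on the DSMB meetings after each block of 50 recruits: "Progress of the trial participants (and any adverse events) and the changes in the primary outcome will be discussed".
- Follow-up of Adverse Events, in full: "We will report any adverse events to the treating medical team as appropriate".

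No part of the protocol defines a serious adverse event, grades severity, asks whether an event was related to exercise or testing, or records whether it resolved. The Safety section places recording at a weekly contact in both groups. The Intervention section and section 6 give the control group a call once a month.

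**The concern.** These participants are being treated for cancer. The Background describes treatment side effects that are common and sometimes debilitating, and some will need a medical review for reasons unrelated to SMART. Because every adverse event is recorded and need for review is the only criterion, such events enter the same class as an exercise injury or a cardiac event during a session. Nothing in the described record would let an analyst separate them later.

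This differs from detail that can be left to a statistical analysis plan. The protocol itself fixes the classes, and a field that was never collected cannot be recovered at analysis. What is at stake is the harm side of the result. The investigators hope to move a similar program into routine care, and clinicians will ask how many serious events occurred in each arm and whether any arose from the exercise. The DSMB, which can raise concerns that would warrant stopping, needs the same information.

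**Working it through.** **1. What the rule does with different events.** Applying the criterion as written:

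| Event | Medical review warranted? | Class |
|---|---|---|
| Muscle soreness after a session | No | Minor |
| Chemotherapy side effect that needs review | Yes | Non-minor |
| Sore knee that needs review | Yes | Non-minor |
| Injurious fall | Yes | Non-minor |
| Cardiac event during a session | Yes | Non-minor |
| Death | Yes | Non-minor |

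The last five differ in seriousness and in plausible link to exercise, but carry the same code.

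**2. Could other data separate them?** The side-effect questionnaires (section 4, Monitoring) ask about effects of both treatment and exercise, but their stated purpose is to adapt the program and they are not tied to the event classes. Emergency visits and inpatient days (section 7, Other variables) are collected in both groups, but by participant recall and without a link to an event record. They are to be summarised by mean and standard deviation. They partly stand in for seriousness and say nothing on relatedness.

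**3. The arm size.** The sample size reproduces: 2 × (1.96 + 0.8416)² × 20.52² / 8² = 103.3, so 104 per group, and 104 / 0.8 = 130 recruited per group. The present point does not affect it.

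**4. Dilution, as an illustration.** The protocol gives no adverse event rate, so the background proportion b with a non-minor event is an assumption, shown over a range. Let SMART add a true excess of 5 percentage points, so p₁ = b and p₂ = b + 0.05, with n = 130 per arm and two-sided α = 0.05. Then

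power = Φ{(0.05 − 1.96 × SE₀) / SE₁}, where SE₀ = √(2p̄(1 − p̄)/n), SE₁ = √((p₁(1 − p₁) + p₂(1 − p₂))/n), and p̄ is the mean of p₁ and p₂.

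- b = 1%: SE₀ = 0.0228, SE₁ = 0.0226, z = (0.05 − 0.0447)/0.0226 = 0.24, power 59%.
- b = 30%: SE₀ = 0.0581, SE₁ = 0.0580, z = (0.05 − 0.1139)/0.0580 = −1.10, power 13.5%.

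| Assumed background | Power for a 5-point excess | Smallest excess with 80% power |
|---|---|---|
| 1% | 59% | 7.3 points |
| 2% | 49% | 8.4 points |
| 5% | 33% | 10.5 points |
| 10% | 23% | 12.9 points |
| 30% | 13.5% | 16.9 points |
| 50% | 12% | 17.1 points |

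The more background events share the class, the less a given excess stands out. Even at 1% the power is only 59%, so the classification worsens a limit that sample size already imposes.

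**5. Ascertainment.** Over 16 weeks, weekly sessions give the SMART arm 16 planned contacts. Monthly calls give the control arm about 4, a ratio of 16/4 = 4. If events are sought at these contacts, one arm is asked four times as often, which conflicts with the weekly recording in both groups stated under Safety.

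**The case against.** The strongest reply is that this is a 1:1 randomised trial with events recorded in both arms. A difference in total non-minor events can be attributed to allocation without any causality coding, and emergency visits and inpatient days are available by arm. Safety is neither a research question nor an endpoint, and the low-risk statement rests on cited literature. All of this stands. It does not supply a count of serious events per arm, because no field identifies them.

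A reader might go further in three ways that the documents do not support.

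- One might infer that treatment events will fill the non-minor class, or put a number on them. No rates are given, and the examples are exercise symptoms, a fall and a cardiac event. Mixing is likely, but dominance is not shown.
- One might infer that the trial cannot say anything about harm from SMART. The randomised comparison of all non-minor events remains possible, so that is too strong.
- One might infer that contact with the medical team turns a minor symptom into a non-minor event, because staff will "modify the program as required and also liaise with the treating medical team". That sentence concerns malaise and soreness. The class depends on whether a review was warranted, and liaising is not a review.

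Nor does the word resolve in the definition of minor necessarily leave an event without a class: a persisting event can be judged to warrant review. What remains is that outcome is not recorded.

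**Conclusion.** The concern holds in a limited form. The two-class scheme does not separate serious or exercise-related events from medically reviewed treatment toxicity. Total non-minor events can be compared between arms, but serious events per arm and harm attributable to SMART will be poorly characterised. The size cannot be fixed from the protocol: the fall in power from 59% to 13.5% rests wholly on assumed background proportions of 1% to 30% and an assumed 5-point excess. The primary outcome and sample size are untouched.

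The conflict between weekly event recording in both groups and monthly control calls is explicit in the text. If controls are in fact asked monthly, it would bias even the randomised comparison of events.

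This is a worthwhile, inexpensive improvement and does not invalidate the design. The REDCap form is not shown. If it already holds these fields, only the protocol wording needs to change.

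**What to change.** Keep the minor/non-minor field and the existing 48-hour ethics committee rule. Add three fields to the REDCap adverse event form, completed for every event in both arms:

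- serious (yes/no), with the definition written into the protocol;
- relation to trial exercise or trial testing (related / possibly / unrelated);
- outcome at last contact (resolved / ongoing).

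Give the DSMB, and report in the results, all-event and serious-event counts by arm as the main comparison, with relatedness as supporting description. Do not make possible relatedness a trigger for 48-hour reporting: post-exercise soreness and malaise, which the protocol lists as minor, are related almost by definition and would all be swept in.

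Reconcile the Safety section with the control contact schedule in the Intervention section and section 6, so that the protocol states one schedule for seeking events in each arm and any difference between arms is acknowledged when events are compared.

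The cost is three fields and a paragraph of protocol text. Relatedness will be judged unblinded and has limited meaning in the control arm, which is why it should not carry the main comparison. The added fields improve description. They will not give the trial power for rare harms, and serious events will still include some caused by cancer treatment.
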